### Sample size

The mean ± SD of baPWV among T2DM patients was 1548.87 ± 305.48 cm/s in Beijing, China (aged 20–80 years) (21), 1580 ± 324 cm/s in Nanchang, China (aged 17–75 years) (22), and 1534.2 ± 254 cm/s in Kagoshima, Japan (aged 22–84 years) (23). Among healthy people, it was 1200 ± 150 cm/s (aged 40–49 years), 1390 ± 190 cm/s (aged 50–59 years), 1630 ± 300 cm/s (aged > 60 years) in Xinjiang, China (24).

Considering that the above data were derived from small-sample studies and the age ranges were not consistent with this study, we hypothesized that the baPWV was 1600 ± 260 cm/s for T2DM patients aged 40–85 years, and YQYYHX was expected to reduce it to 1440 ± 234 cm/s (25, 26). A change of 100 cm/s may represent a minimal clinically important difference (27). This study is designed by superiority, and the ratio between the treatment and control groups is 1:1. With a two-sided α = 0.05 and β = 0.1, the sample size is calculated to be 52 in each group using a *t*-test allowing unequal variances in PASS 15. The formula is as follows.

$$\begin{array}{l} n=\frac{{\left(Z_{1-\alpha /2}\;+\;Z_{1-\beta }\right)}^{2}\cdot 2\sigma^{2}}{{\left(\mu_{1}-\mu_{2}\right)}^{2}} \end{array}$$

Considering a 10%−15% dropout rate, 60 patients are needed in each group and the total sample size is 120.

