### Outcomes

Participants who take the granules for more than 80% of the expected duration will undergo the following assessments before and after the 12-week treatment.

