### Statistical plan

#### Analysis sets

The full analysis set (FAS) includes all participants who were randomized, using their last observed data as the trial outcome for intention-to-treat analysis. The per-protocol set (PPS) refers to participants who strictly adhered to the trial protocol, demonstrated good compliance, did not take prohibited medications during the trial, and completed the required case report forms. It will be utilized for the primary efficacy analysis. The safety set (SS) comprises all participants who were randomized, received at least one dose of the study treatment, and have post-treatment safety data available. Statistical descriptions and analyses of their safety outcomes and adverse event incidence will be performed.

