### Conditions for suspension, drop-out and termination

In accordance with medical standards, participant safety considerations, and GCP requirements, investigators will determine whether a participant needs to suspend or drop-out. Participants will be classified as drop-out if they are newly diagnosed with other diseases that may influence the trial, if they begin using other traditional Chinese medicines with similar therapeutic effects, or if they are lost to follow-up during the observation period.

An adverse event refers to any unfavorable medical occurrence during the study, regardless of whether it is causally related to the intervention. It includes clinically significant abnormalities in electrocardiogram, liver function, or renal function tests, as well as any subjective symptoms of discomfort reported by the participants. If it occurs, investigators should record, assess the severity and the relationship with the trial, and observe until returning to normal. A serious adverse event is any unfavorable medical occurrence that result in hospitalization, disability, incapacity, or even life-threatening conditions. It requires immediate medical management plus immediate reporting to the principal investigator once known, followed by expedited reporting to the ethics committee. If more than half of the participants experience serious adverse events, the trial must be terminated.

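### The safety set requires post-treatment safety data, an undefined condition that can remove dosed participants who stop early from the adverse-event rates

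*Protocol article*

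**What the plan says.** Under Analysis sets, the safety set has three conditions: randomisation, at least one dose, and available data. Members are those who "received at least one dose of the study treatment, and have post-treatment safety data available". The next sentence makes this the set for adverse events as well as tests: "Statistical descriptions and analyses of their safety outcomes and adverse event incidence will be performed".

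The Outcomes section opens with a sentence that governs the lists below it: "Participants who take the granules for more than 80% of the expected duration will undergo the following assessments before and after the 12-week treatment". One of those lists is Safety outcomes: electrocardiogram, blood count, liver and renal function, and urinary albumin-to-creatinine ratio.

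The section on suspension, drop-out and termination defines adverse events widely. They include clinically significant ECG, liver and renal abnormalities, "as well as any subjective symptoms of discomfort reported by the participants". Investigators must record each event, assess it and follow it until it resolves. That section sets no adherence condition. It also says that, with participant safety among the grounds, "investigators will determine whether a participant needs to suspend or drop-out".

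**The concern.** The third condition is met or failed after dosing, and whether a participant meets it may depend on how well the treatment was tolerated. Someone who stops early is below the 80% threshold. On the literal text of Outcomes, that person has no scheduled post-treatment safety tests, and may then fail the data condition and drop out of the adverse-event calculation altogether.

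A safety set of dosed participants with some post-dose data is common and often nearly harmless. Here it sits beside an adherence rule that appears to decide who is tested. Safety is a stated aim of the trial, and the arms are small: 60 each. A handful of exclusions linked to harm would change the reported rate visibly, and randomisation gives no protection because the exclusion happens after dosing.

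**Working it through.** **The plan's own figures.** Sample size supplies the denominators, so I checked it first. The section states that "the sample size is calculated to be 52 in each group using a" t-test allowing unequal variances, from 1600 ± 260 against 1440 ± 234 cm/s, two-sided α = 0.05 and β = 0.1.

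- Normal approximation: (1.960 + 1.282)² × (260² + 234²) / 160² = 10.51 × 122,356 / 25,600 = 50.2, so 51 per group.
- Unequal-variance t-test (noncentral t): power 0.899 at 51 and 0.904 at 52, so 52 per group. The stated figure reproduces.
- Dropout: 52 / 0.90 = 57.8, so 58; 52 / 0.85 = 61.2, so 62. The stated 60 lies between them. No stated figure is in dispute.

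**Most who could be affected.** The plan allows for a 10% to 15% "dropout rate, 60 patients are needed in each group and the total sample size is 120". That is 0.10 × 60 = 6 to 0.15 × 60 = 9 per arm, or 12 to 18 in total. This is a ceiling, reached only if no drop-out has any qualifying safety data.

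**Effect on the reported rate.** Let n be the number dosed, x those with a true event, k those excluded for lack of data, and h the excluded who had an event.

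- All dosed participants: x / n
- Safety set as written: (x − h) / (n − k)

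The second is too low when h/k exceeds x/n, too high when h/k is smaller, and unchanged when they are equal. The documents give none of x, k or h. I assume n = 60 and x = 6, a true rate of 6/60 = 10.0%.

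| Excluded (k) | Of these, with an event (h) | Reported rate |
|---|---|---|
| 3 | 3 | 3/57 = 5.3% |
| 6 | 0 | 6/54 = 11.1% |
| 6 | 3 | 3/54 = 5.6% |
| 6 | 6 | 0/54 = 0% |
| 9 | 0 | 6/51 = 11.8% |

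The scope for error is lopsided. With six excluded, the rate can rise by about 1 percentage point or fall by up to 10.

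**Effect on the arm comparison.** Suppose both arms have a true rate of 6/60 and six exclusions each.

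- Three of the excluded had an event in each arm: 3/54 against 3/54, so no false difference.
- Three had an event in the granule arm and none in the placebo arm: 3/54 = 5.6% against 6/54 = 11.1%, a false advantage of 3/54 = 5.6 percentage points for the granules.
- The reverse pattern gives the same false difference against the granules.

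**Which participants are excluded.** This depends on what counts as post-treatment safety data.

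- *End-of-treatment tests.* The before-and-after-12-weeks timing in Outcomes points this way. Early stoppers fail the condition, including those with a recorded event.
- *Any safety information after the first dose.* A recorded adverse event then qualifies. Those excluded are mainly people lost before any contact. Laboratory or ECG abnormalities in early stoppers may still go unmeasured if the 80% rule is followed literally.

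Nothing shown in the article chooses between the two.

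**The case against.** The strongest reply is that the condition is harmless on a natural reading. The safety set serves adverse events as well as tests, so safety data need not mean the test battery. The drop-out section requires every event to be recorded and followed, whatever the adherence. A participant who stops because of an event therefore has safety data after dosing and stays in. The 80% sentence cannot be literal either, since it would make the baseline assessment depend on later adherence. The schedule in Table 1 is not shown and may contain interim visits.

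Much of this stands. A reader might infer that withdrawals for harm necessarily vanish from the rates. The documents do not support that, because a recorded event may satisfy the condition. A reader might also infer that the rule favours the granules. It applies alike to both blinded arms, and nothing in the article shows more harm-related exclusions in one of them. Nor will 12 to 18 participants necessarily be lost: the drop-out reasons include new diagnoses and use of other traditional medicines, which do not imply absent safety data.

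The ambiguity remains. The text permits two readings that yield different adverse-event rates. Even the favourable one leaves laboratory and ECG harm in early stoppers exposed to the 80% sentence.

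**Conclusion.** The concern holds as a defect in a stated rule, of moderate weight. The safety set adds a data-availability condition that is undefined, depends on what happens after dosing, and sits beside an adherence restriction on the safety tests. The narrow reading can remove early stoppers from the incidence; the broad reading confines the loss mainly to people never contacted and abnormalities never measured.

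The size rests on assumptions. With a 10% true rate, 60 dosed and 6 excluded, the reported rate runs from 0% to 11.1%: too low when exclusion is linked to harm, slightly too high when those excluded had no events. Bias towards the granules would need harm-related exclusions to be more frequent in that arm, and this is not shown.

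**What to change.** 1. Define the safety set as all randomised participants who took at least one dose, with no condition on post-treatment data.
2. Count every recorded adverse event over that denominator.
3. Summarise laboratory and ECG values on available data, with the number missing by arm.
4. Reconcile the 80% sentence in Outcomes with Safety outcomes, Analysis sets and the drop-out section, so that adherence does not decide who contributes safety data. The first three changes alone would leave this restriction in place.

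The cost is a few lines of text and no added sample size. On 10 March 2026 the trial had 72 enrolled and 38 who had completed observation. The main analysis follows unblinding, and interim results go only to the monitoring committee, so the trial team can make the change blinded. The drawback is that a dosed participant with no later contact counts as having no recorded event. The missing counts by arm make that visible.

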#### Interim analysis

A group sequential design will be adopted for statistical inference, with a prespecified interim analysis to be conducted when approximately 50% of the total information for the primary endpoint has accrued. Interim analysis results and unblinded data will be accessible only to the independent Data Monitoring Committee, which will mainly consist of statisticians, clinical and ethics experts.

An O'Brien-Fleming efficacy boundary will be applied to control the overall two-sided type I error rate at 0.05, using the Lan-DeMets alpha-spending function as an approximation. Statistical significance will be determined on the basis of the prespecified nominal significance level corresponding to each analysis. If the baPWV crosses the prespecified efficacy boundary at an interim analysis, early termination of the trial may be recommended.

#### Outcome analysis

All data will be analyzed using SPSS 26.0 after unblinding. Continuous outcomes will be initially assessed for distributional characteristics by Shapiro-Wilk test. For approximately normally distributed outcomes, *t*-tests or ANCOVA will be applied to compare groups; for variables with marked deviation from normality, nonparametric alternatives such as the Mann–Whitney *U*-test and Wilcoxon signed-rank test will be considered. The categorical variables will be analyzed using the χ^2^ test.

Baseline covariates and other prognostic factors will be incorporated into ANCOVA models to improve estimation precision and control for residual confounding. Repeated measurements or longitudinal data will be analyzed using linear mixed-effects models, allowing for appropriate modeling of within-subject correlations, and evaluation of treatment-by-time interactions. The hierarchical testing procedure will be used to adjust multiple secondary outcomes. Sensitivity analysis will be conducted to reduce the impact of protocol deviations.

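### No single primary test is fixed for baPWV: a normality check and an open choice between t-test and ANCOVA decide after unblinding whether baseline is adjusted for

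*Protocol article*

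**What the plan says.** The Outcome analysis section opens with "All data will be analyzed using SPSS 26.0 after unblinding" and continues with "Continuous outcomes will be initially assessed for distributional characteristics by Shapiro-Wilk test". It then branches:

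- **Approximately normal:** t-tests or ANCOVA. No criterion chooses between the two.
- **Markedly non-normal:** "nonparametric alternatives such as the Mann–Whitney" U-test and the Wilcoxon signed-rank test are to be considered. No threshold defines how marked the departure must be.

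The same section says that baseline covariates and prognostic factors enter the ANCOVA models, but it names none and does not make ANCOVA primary. It also assigns linear mixed models to repeated or longitudinal data without saying whether baPWV, measured before and after treatment, counts as such.

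BaPWV is the sole primary outcome. The Interim analysis section applies a Lan-DeMets/O'Brien-Fleming boundary to it: the "efficacy boundary will be applied to control the overall two-sided type I error rate at 0.05". The test statistic that the boundary applies to is not defined. The Sample size section uses an unadjusted unequal-variance t-test.

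**The concern.** A confirmatory trial needs one primary test that does not depend on the unblinded data. Here two decisions stay open until the codes are available: whether the data are normal enough, and, if they are, which of two parametric tests to use. Those two tests give different p-values from the same data, so the promised overall 0.05 holds only if the choice is made without regard to the results.

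The second stake is precision. Baseline baPWV is measured in any case, and it is likely to predict the week-12 value. It is used on the ANCOVA branch and ignored on the t-test and Mann-Whitney branches. This matters most at the smaller effect that the plan itself mentions: "A change of 100 cm/s may represent a minimal clinically important difference".

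**Working it through.** **Inputs (Sample size section).** "two-sided α = 0.05 and β = 0.1"; "we hypothesized that the baPWV was 1600 ± 260 cm/s for T2DM patients aged 40–85 years"; "YQYYHX was expected to reduce it to 1440 ± 234 cm/s"; 52 evaluable per arm. The design difference is 1600 − 1440 = 160 cm/s, and the smallest important difference is 100 cm/s. The baseline-to-week-12 correlation ρ is not given, so it is an assumption, shown from 0.3 to 0.7.

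**Step 1: reproduce the plan's figure.** SE = √[(260² + 234²)/52] = √(122,356/52) = √2,353 = 48.51 cm/s, and 160/48.51 = 3.30. Welch power from the noncentral t is 89.9% at 51 per arm and 90.4% at 52. The stated 52 is correct.

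**Step 2: power with baseline adjustment.** ANCOVA multiplies the SE by √(1 − ρ²).

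| ρ (assumed) | √(1 − ρ²) | SE, cm/s | Power at 160 cm/s | Power at 100 cm/s |
|---|---|---|---|---|
| unadjusted | 1 | 48.51 | 90.4% | 53.3% |
| 0.3 | 0.954 | 46.27 | 92.8% | 57.2% |
| 0.5 | 0.866 | 42.01 | 96.5% | 65.5% |
| 0.6 | 0.800 | 38.81 | 98.3% | 72.3% |
| 0.7 | 0.714 | 34.64 | 99.6% | 81.6% |

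The gain is 2 to 9 points at 160 cm/s and 4 to 28 points at 100 cm/s.

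**Step 3: type I error.** All figures are for one look at 5% with 52 per arm; the two-look version was not computed.

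- One fixed ANCOVA: 4.5-5.1% in simulation.
- A mechanical two-stage rule (Shapiro-Wilk in each arm at 5%, then one named test per branch): 4.6-5.3%.
- Better of t-test and ANCOVA when normality passes, Mann-Whitney when it fails, normal data: 6.6% at ρ = 0.5 and about 8% at ρ = 0.7 (7.9% and 8.2% in two sets of runs).

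The last result can be checked without simulation. In SD units, the unadjusted estimate is D and the adjusted one is D − ρB, where D and B are the between-arm differences in outcome and baseline. Their covariance is 1 − ρ² and the adjusted variance is 1 − ρ², so the two test statistics correlate at √(1 − ρ²). For a standard bivariate normal pair with that correlation, the chance that either exceeds 1.96 in absolute value is 6.4%, 7.3%, 7.8% and 8.3% at ρ = 0.3, 0.5, 0.6 and 0.7. This agrees with the simulation.

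**Step 4: skewed data.** Simulated power at 100 cm/s, log-normal-type data:

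- Moderate skew (Shapiro-Wilk rejects in at least one arm in about 83% of trials), ρ = 0.7: ANCOVA 81%, two-stage rule with ANCOVA on the parametric branch 63%.
- Strong skew (rejection in over 99%), ρ = 0.7: ANCOVA 80%, Mann-Whitney 72%.
- Strong skew, ρ = 0.5: ANCOVA 63%, Mann-Whitney 71%. The order reverses.

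**The case against.** The strongest reply is that each between-group test is valid on its own, that the t-test matches the sample-size calculation, that covariate adjustment is already foreseen, and that an analysis plan not shown here may name the primary test. Analysing after unblinding is routine, because a comparison of arms needs the codes.

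Much of this stands. But the article does more than leave the test unnamed. It prints a rule in which the data, and then an unguided choice, select the test for the primary outcome. An analysis plan that fixed one test would depart from that rule. The covariate sentence helps only once ANCOVA has been chosen.

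A reader might infer several stronger claims that the documents do not support:

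- **That the Shapiro-Wilk step itself inflates the error rate, or chooses between t-test and ANCOVA.** It only separates parametric from rank methods, and applied mechanically it keeps type I error near 5%.
- **That adjustment always adds much power.** At 160 cm/s power is already 90%. At 100 cm/s the gain is only 4 points if ρ is 0.3, and entry selection on raised PWV could lower ρ.
- **That a known share of trials would be sent to rank tests.** Any such figure needs an assumed distribution and an assumed cut-off, and the article states neither.
- **That the signed-rank test is planned as evidence of efficacy.** It appears in a generic paragraph and is an ordinary paired test. The trial is designed as a between-group superiority comparison.
- **That the statistic will change between the interim and the end.** The text permits this but does not plan it.

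**Conclusion.** The point holds in a limited form. The printed rule does not fix one primary test for baPWV, and baseline adjustment depends on which test is picked. If the better of t-test and ANCOVA were reported, the false-positive rate would be about 7-8% for ρ of 0.5-0.7 instead of 5%. Nothing in the article says that anyone would do so; the fault is that the rule allows it.

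At 52 per arm, fixing a baseline-adjusted ANCOVA gives 93-99.6% power at 160 cm/s against 90%, and 57-82% at 100 cm/s against 53%. These ranges rest on assumed correlations of 0.3-0.7, the plan's SDs and approximate normality. Under strong skew with a moderate correlation, a rank test can be more powerful. The sample size of 52 per arm is not in question.

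**What to change.** Before the interim analysis and any unblinding, amend the Outcome analysis and Interim analysis sections:

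1. Name ANCOVA of week-12 baPWV on treatment and baseline baPWV as the single primary analysis at both looks, reported as an adjusted mean difference with a confidence interval. List any further covariates by name.
2. Remove the normality gate for the primary outcome.
3. Prespecify a log-scale or rank-based ANCOVA as a sensitivity analysis, to cover skew.
4. State that within-group tests, including the Wilcoxon signed-rank test, are descriptive only.

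The cost is a wording amendment, one degree of freedom, and possibly some power if baPWV proves strongly skewed. No new data or participants are needed, because baPWV is already measured before and after treatment. The Trial status section reports 38 completers at 10 March 2026. Half of the 2 × 52 = 104 evaluable participants is 52, so on that count the interim had not yet been reached at that date.

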## Methods

### Study design

This study is a single-center, randomized, double-blind, placebo-controlled, parallel-group clinical trial. The trial is designed in accordance with contemporary SPIRIT guidance (15). The SPIRIT schedule is shown in Table 1, and the study flowchart is shown in Figure 1.

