### Diagnostic criteria

1. Diagnostic criteria for T2DM

In the presence of classic symptoms of hyperglycemia, such as polyuria, polydipsia, polyphagia, or unexplained weight loss, the diagnosis of T2DM can be established when any one of the following criteria is met (16):

Random blood glucose (BG) ≥ 11.1 mmol/L;

Fasting BG ≥ 7.0 mmol/L;

2-hour BG ≥ 11.1 mmol/L during a standard oral glucose tolerance test;

Glycated hemoglobin (HbA1c) ≥ 6.5%.

2. Diagnostic criteria for EVA

Age-adjusted pulse wave velocity (PWV) exceeds the upper limit of normal for healthy individuals by more than two standard deviations (17, 18).

3. Fontaine stage I - IIA classification

Stage I: Asymptomatic.

Stage IIA: Mild intermittent claudication; walking distance > 200 meters (19).

4. Diagnostic criteria for Qi-Yin deficiency with blood stasis syndrome

“Qi-Yin deficiency with blood stasis” syndrome can be diagnosed when either two primary symptoms or three secondary symptoms are present, accompanied by characteristic tongues and pulses.

Primary symptoms: Dry throat and mouth; shortness of breath with reluctance to speak; limb numbness; stabbing pain in the extremities.

Secondary symptoms: limb weakness; spontaneous or nocturnal sweating; heat sensation in the palms and soles; palpitations and insomnia; rough or dry skin; purplish lips; constipation or diarrhea.

Tongue and pulse characteristics: Pale-dark tongue or presence of ecchymoses; tortuous cyanotic sublingual veins; white coating. Pulse may be thin, deep, wiry, or choppy.

5. Absolute Contraindications for the 6MW

Unstable angina and myocardial infarction during the previous month (20).

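### The Wilcoxon signed-rank test is listed as an alternative to the between-arm tests without a role of its own, although here it can only assess change within one arm, and non-normal outcomes lose baseline adjustment (minor)

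*Protocol article*

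**What the plan says.** The article describes two independent arms: "This study is a single-center, randomized, double-blind, placebo-controlled, parallel-group clinical trial". The objective is between-arm. Under Sample size it states: "This study is designed by superiority, and the ratio between the treatment and control groups is 1:1". Under Outcomes, participants "will undergo the following assessments before and after the 12-week treatment", so the only pairing in the data is baseline with week 12 in the same person.

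Under Outcome analysis, approximately normal continuous outcomes go to t-"tests or ANCOVA will be applied to compare groups; for variables with marked deviation from normality", and the sentence continues, "nonparametric alternatives such as the Mann–Whitney *U*-test and Wilcoxon signed-rank test will be considered". It gives the signed-rank test no purpose apart from the tests it replaces.

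The next paragraph puts baseline covariates into ANCOVA models, uses mixed models for repeated measurements with treatment-by-time interactions, and applies a hierarchical procedure to the secondary outcomes. It names no baseline-adjusted method for the non-normal branch and does not say which test feeds the hierarchy.

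**The concern.** An alternative to a test that compares arms should itself compare arms. Mann-Whitney does. The signed-rank test needs pairs, and its null here is no change from baseline within the arm analysed. Placebo data do not enter it.

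The distinction has practical weight in this trial because both arms may improve without any treatment effect. Entry requires an age-adjusted PWV that "exceeds the upper limit of normal for healthy individuals by more than two standard deviations", together with a symptom-defined TCM syndrome. Selection on high values produces regression to the mean, and questionnaire outcomes can add placebo response. The outcomes most likely to reach the non-parametric branch are cytokines, triglycerides and symptom scores. If a within-arm p-value for one of these were read as efficacy, improvement common to both arms would be credited to YQYYHX.

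A second, quieter loss is precision. Normal outcomes are adjusted for baseline through ANCOVA. Non-normal outcomes go to a Mann-Whitney test that takes no covariate, and the article does not say whether it is applied to week-12 values or to change.

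**Working it through.** **1. The plan's own figure.** Sample size gives means 1600 and 1440 cm/s, SDs 260 and 234, two-sided α = 0.05 and β = 0.1. The normal approximation is n = (1.960 + 1.282)² × (260² + 234²) / 160² = 10.51 × 122,356 / 25,600 ≈ 50.2, so 51. The unequal-variance t-test gives power 0.899 at 51 and 0.904 at 52. The stated 52 per arm is reproduced. The present point does not depend on it; 52 and SD 260 are used below only for scale.

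**2. What each test addresses.** Let D = week 12 minus baseline.
- Mann-Whitney on D (or on week-12 values): the null is that the two arms have the same distribution. This is the superiority question.
- Signed-rank on D in one arm: the null is that D is symmetric about zero in that arm. An equal fall in both arms violates it while the between-arm null is true.

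**3. Illustration of the gap.** The article gives neither the baseline to week-12 correlation r nor any common fall, so both are assumed. SD of D = 260 × √(2(1 − r)). At r = 0.8 this is 260 × √0.4 = 164 cm/s, and the standard error of the mean with 52 participants is 164/√52 = 22.8. A fall of 50 cm/s is therefore 2.2 standard errors.

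Simulation with 52 per arm, no difference between arms, two-sided 0.05:

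| Common fall (cm/s) | Signed-rank in YQYYHX arm, r = 0.5 / 0.7 / 0.8 | Mann-Whitney between arms |
|---|---|---|
| 0 | about 5% throughout | about 5% |
| 50 | 26% / 40% / 55% | about 5% |
| 100 | 75% / 93% / 99% | about 5% |

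The pattern of a significant result in YQYYHX but not in placebo has probability p(1 − p) when the arms are independent and share the rejection rate p. Its maximum is 0.5 × 0.5 = 25%.

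**4. Could a common fall of this order arise?** For a population of 1600 ± 260 with entry above 1600, the mean fall from regression to the mean is (1 − r) × 260 × φ(0)/0.5 = (1 − r) × 260 × 0.798. That is 62, 41 and 21 cm/s at r = 0.7, 0.8 and 0.9. Simulated signed-rank rejection is then 60%, 42% and 25%. With entry above 1400 it is 18%, 13% and 9%. Both cut-offs are illustrative, because the article's EVA threshold is age-adjusted and 1600 is its hypothesised patient mean, not an entry limit.

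**5. What baseline adjustment is worth.** Relative to week-12 values alone, the between-arm variance is multiplied by 2(1 − r) for change and by (1 − r²) for covariate adjustment. At r = 0.5 these factors are 1.00 and 0.75; at r = 0.8, 0.40 and 0.36; at r = 0.9, 0.20 and 0.19. By simulation with 52 per arm and a true difference of 100 cm/s (the article's minimal clinically important difference), Mann-Whitney on week-12 values has 46–49% power. Baseline-adjusted rank ANCOVA has just under 60% at r = 0.5, rising to about 98% at r = 0.9, with type I error near 5%. These runs also use normal data, so they show direction and rough size, not the gain for any particular skewed outcome.

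**The case against.** The case against is substantial.

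- Grammatically, the purpose of comparing arms attaches to the clause before the semicolon. The plural t-tests can cover independent and paired forms, whose usual non-parametric counterparts are Mann-Whitney and signed-rank, in that order. The ordinary reading is therefore Mann-Whitney between arms and signed-rank for before-after change. This stands as the likely intention, but the article does not state it.
- Paired analysis has a natural place elsewhere: the serum omics use 30 treatment-arm participants only, with samples from before and after treatment. That section has its own analysis statement and does not name signed-rank, so it does not settle the test's role under Outcome analysis.
- The wording is permissive, the valid Mann-Whitney test is named first, and ANCOVA and mixed models are between-arm methods. This stands and limits the severity.
- The rejection rates in steps 3 and 4 are power to detect an assumed real within-arm change. They were computed on normally distributed baPWV, which under this plan would go to a t-test or ANCOVA. This also stands.
- A condensed article may leave the assignment of tests to the full protocol or analysis plan. That would excuse silence, but here the article itself lists the test in a place where it does not fit.

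A reader might infer that the trial will declare efficacy from a before-after p-value, or that its false-positive rate is 40% or more. The document supports neither. No sentence lets a within-arm result, or significance in one arm and not the other, count as efficacy or enter the secondary hierarchy.

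**Conclusion.** The point holds as a minor defect of specification. As written, the signed-rank test appears among the alternatives to the between-arm tests, which it cannot replace in a parallel-group trial, and nothing in the article gives it a separate or descriptive role. The non-normal branch also has no baseline-adjusted method, while the normal branch has one.

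The simulated signed-rank rates (for example 26–55% for a 50 cm/s common fall at assumed correlations of 0.5 to 0.8) are an illustration. They apply only if a within-arm p-value is read as efficacy, and they are not the error rate of the planned analysis. The precision gain from baseline adjustment does not depend on how the sentence is read, but its size depends on the assumed correlation.

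**What to change.** Amend the Outcome analysis text as follows:

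- Remove the signed-rank test from the between-arm methods.
- For markedly non-normal outcomes, name baseline-adjusted rank ANCOVA as the between-arm method, or else Mann-Whitney on change with a Hodges-Lehmann difference and 95% CI. Rank ANCOVA is the more efficient when the correlation is modest: at r = 0.5, change gains nothing over week-12 values.
- State that every efficacy conclusion, including each step of the secondary hierarchy, rests on the between-arm contrast.
- Label any within-arm before-after result as descriptive.

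The cost is a few lines of wording, with no new data or participants. Rank ANCOVA needs only ranking and linear regression. The one thing given up is the use of within-arm p-values as evidence, and they do not address superiority. With 72 enrolled and 38 completed at the last report, the change can still be made cleanly if it precedes any unblinded analysis.
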